## Method/design

### Design and participants

We will employ a SW-RCT with 30 outpatient SUD treatment clinics who serve approximately 2000 clients with OUD per year to test whether CARE improves treatment process quality and recovery outcomes over treatment as usual. The study will benefit from multiple sources of data to test study aims, including state administrative data, client-reported survey and eTPA8 data, and staff interview and survey data. Therefore, this will be a robust study of the implementation of a measures-driven QI approach for SUD treatment. Figure 2 shows the stepped-wedge design. Five clinics will start CARE every 6 months over 3 years; therefore, there are 6 steps, each with 5 clinics randomly assigned to 1 of the 6 steps.

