### Analysis and power

The primary aim of this study is to test whether CARE is associated with greater use of pharmacotherapy for OUD, longer retention in care, and improved recovery outcomes (e.g., reduced drug use). We will employ multiple convergent analytical methods to (a) examine CARE implementation and (b) test association between CARE and OUD treatment outcomes. Analyses will begin with examination of distributions of variables and transformations where appropriate, examination of patterns of missingness, and application of formal imputation methods [77–79] if deemed essential to project aims. Analyses for Aims 1, 2, and 3 will utilize general linear mixed models (GLMM) for stepped-wedge designs [80–85]. For example, to test the effect of CARE on treatment process quality measures (i.e., initiation and adherence to OUD medications, in-treatment symptom and therapeutic progress, 6-month treatment retention) and recovery outcomes (substance use, overdoses, self-reported health status, HCV infection, and ED visits), we will employ stacked difference-in-difference models that test for within and across clinic changes while adjusting for secular trends across time [80, 86, 87]. The models will take the form: *Y*_*ikt*_ = *μ* + *X*_*kt*_*θ* + *β*_*t*_ + *Z*_*ikt*_ + *α*_*k*_ + *e*_*ikt*_, where *β*_*t*_ is a fixed effect for time, *Z*_*ijk*_ is a matrix of covariates measuring individual, geographical, and clinic characteristics for person *i* in clinic *k* at time *t, X*_*kt*_ is an indicator for intervention in clinic *k* at time *t* (coded 0 for baseline then 1 from when intervention begins in clinic through end of study), and *θ* is the treatment effect. *Y*_ikt_ represents a matrix of binary variables: treatment process quality measures (i.e., pharmacotherapy initiation and adherence, in-treatment symptom and therapeutic progress, treatment retention) and recovery outcomes (i.e., substance use, overdoses, self-reported status, HCV infection, and ED visits). We will estimate the effect of CARE (*θ*) while controlling for secular trends (*β*) and adjusting for clustering within clinic (*α*_*k*_) using robust standard errors. We will also conduct a set of falsification tests. These will include (1) testing for variation in program and client characteristics across time of enrollment; (2) examination of variation across study time in the study outcomes for clinics not participating in the study; and (3) examination of variation in intervention effect based on clinics’ baseline levels of quality measures (e.g., comparing top third to bottom third in quality of care at baseline).

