To estimate study power for select outcomes, we drew from methods developed by Hussey and Hughes [80] as implemented in a Stata command, stepped wedge [98]. Using administrative data to estimate sample sizes and baseline rates (μ), we computed detectable differences for a β = 0.80, α = 0.01, ICC/ρ = 0.20, and SW-RCT with 6 crossover points, and 5 clinics randomized at each point. For 6-month retention, assuming step samples sizes (*m*_k_) of 132 and base rate (μ) of 25%, we will be able to find a 2.8pp change in retention (i.e., 27.8%) to be statistically significant and clinically meaningful. We also conducted sensitivity analyses varying ρ (0.10–0.30) and β (0.90) and found detectable differences ranging from 2.6 to 3.2%. For OUD medication initiation, we assume *m*_k_ = 40 Medicaid clients with OUD, μ = 0.40, and find a detectable difference of 6.7%. For ED visits, we assume *m*_k_ = 79 Medicaid clients and μ = 0.40, and find a detectable difference of 3.9%. Consequently, with 30 clinics and 6 steps in our SW-RCT, we will have power to detect moderate and clinically meaningful differences in outcomes.

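### Robust standard errors on 30 clinics need a named small-sample correction and reference distribution; the ordinary version with normal critical values would be anti-conservative

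*Protocol article*

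**What the plan says.** Under Analysis and power, the article announces that "Analyses for Aims 1, 2, and 3 will utilize general linear mixed models (GLMM) for stepped-wedge designs". It then displays a model with fixed period effects, a clinic term and a clinic-level indicator for CARE. Inference on the CARE effect is described as "adjusting for clustering within clinic (*α*_*k*_) using robust standard errors". The operative words are "using robust standard errors". The article does not say which version of the robust estimator is meant, what distribution the test statistic is referred to, or at what level the test is made.

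The design gives few clusters: under Design and participants, "We will employ a SW-RCT with 30 outpatient SUD treatment clinics", and "there are 6 steps, each with 5 clinics randomly assigned to 1 of the 6 steps". The only significance level in the article is an input to the power calculation: "we computed detectable differences for a β = 0.80, α = 0.01, ICC/ρ = 0.20" (the 0.80 printed as β is evidently power).

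**The concern.** The sandwich estimator is justified for a large number of clusters. With 30 clusters, seven period effects and an exposure that varies only at clinic level, two things go wrong in its ordinary form. Residuals are shrunk by the fit, so the variance is biased downward. The variance estimate is also itself noisy, so a normal reference is too narrow. Both errors act in the same direction: intervals are too short and the null is rejected too often. The displayed model is offered for the whole set of Aim 1 process and recovery outcomes, so the choice affects many tests.

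**Working it through.** **Step 1. Reproduce the plan's own figure and see which reference distribution it uses.** Inputs from Analysis and power: "132 and base rate (μ) of 25"%, ICC 0.20, alpha 0.01, power 0.80. From Design and participants: I = 30 clinics, 6 steps of 5. Assumed: T = 7 windows, one of them all-control (the design figure is not shown), and a two-sided test.

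Hussey-Hughes variance, with X the clinic-by-window exposure indicator:

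Var = I·s²(s² + T·τ²) / [(I·U − W)s² + (U² + I·T·U − T·W − I·V)τ²]

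- U (sum of X) = 5(6+5+4+3+2+1) = 105
- W (sum of squared window totals) = 25+100+225+400+625+900 = 2275
- V (sum of squared clinic totals) = 5(36+25+16+9+4+1) = 455
- Total variance 0.25 × 0.75 = 0.1875; τ² = 0.20 × 0.1875 = 0.0375; s² = 0.15/132 = 0.001136
- Numerator: 30 × 0.001136 × (0.001136 + 0.2625) = 0.008988
- Denominator: 875 × 0.001136 + 3500 × 0.0375 = 132.24
- SE = √(0.008988/132.24) = 0.00824
- Detectable difference, normal: (2.576 + 0.842) × 0.00824 = 0.0282

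This agrees with the article: "we will be able to find a 2.8pp change in retention (i.e., 27.8"%). The stated sensitivity range of 2.6 to 3.2 also reproduces when one input is varied at a time (ICC 0.30: 2.64; ICC 0.10: 2.98; power 0.90: 3.18). The power calculation therefore rests on normal critical values. With t on 28 df it becomes (2.763 + 0.855) × 0.00824 = 0.0298, about 3.0 points.

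**Step 2. The reference distribution alone.** If the statistic in truth followed t with 28 df, comparing it with 2.576 would reject with probability 1.56% at a nominal 1%. Downward bias in the variance comes on top.

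**Step 3. Null simulation.** Same 6 × 5 design, seven windows, ICC 0.20, no CARE effect, exchangeable GLS, standard errors clustered on clinic, 100,000 data sets per row (Monte Carlo standard error at 1.9%: √(0.019 × 0.981/100,000) = 0.04 points). Mean clients per clinic-window is 132 except in the last row, which uses about 2000/30/2 = 33. Clinic-size variation (CV) and cluster autocorrelation are assumptions; the article gives neither. Rejection at a nominal two-sided 1%:

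| Size CV | Autocorrelation | Plain, normal | G/(G-1), normal | G/(G-1), t(29) | Kauermann-Carroll, t(28) |
|---|---|---|---|---|---|
| 0 | 1 | 1.92% | 1.72% | 1.14% | 0.99% |
| 0 | 0.8 | 1.88% | 1.72% | 1.12% | 0.97% |
| 0.4 | 1 | 2.06% | 1.88% | 1.27% | 1.07% |
| 0.4 | 0.8 | 2.20% | 1.99% | 1.34% | 1.15% |
| 0.8 | 1 | 2.38% | 2.18% | 1.50% | 1.19% |
| 0.8 | 0.8 | 3.03% | 2.79% | 1.93% | 1.49% |
| 0.4 (33 clients) | 1 | 1.91% | 1.72% | 1.18% | 1.02% |

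Other settings for the plain sandwich with normal reference at a nominal 1%, equal clinics: clinic fixed effects 1.86% to 1.93%; binary outcomes with the article's sample sizes and base rates (plus a smaller sample of 26) 1.74% to 2.02%; working independence 2.26% to 2.31%. At a nominal 5%, the plain sandwich with normal reference rejects in 6.7% to 7.9% of data sets. Kauermann-Carroll with t(28) gives about 5% there (4.8% to 5.4% across runs).

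**The case against.** The strongest reply is that the article never says the standard errors are uncorrected or referred to the normal distribution. *Robust standard errors* names a family that includes the corrected versions, and a journal article may leave the choice within the family to the full protocol or SAP. That stands. A reader might infer that the plan has adopted the uncorrected estimator and so fixed a wrong error rate; the text does not support this. The normal critical values found in Step 1 belong to the power calculation and do not settle how the analysis will be done.

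A reader might also infer that the false-positive rate doubles at the trial's own 1% level. The article states 0.01 only as a power input and gives no level for the analysis. At 5% the inflation is 1.3- to 1.6-fold (6.7/5 to 7.9/5), not double. Nor does the sentence necessarily govern every Aim 1 result: the displayed model is introduced as an example, among several analytical approaches.

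It is also true that a modest default, G/(G-1) with t(29), removes most of the excess when clinics are of similar size. It does less when sizes differ. The article sets only a floor on clinic size (50 OUD clients a year), so equal sizes cannot be taken for granted.

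What remains is that the article does name its variance method, and the unqualified name covers versions that perform noticeably differently with 30 clusters.

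**Conclusion.** The point holds as a conditional and inexpensive improvement. Carried out as the ordinary sandwich with normal critical values, the stated method has a type I error of about 6.7% to 7.9% at a nominal 5%, and about 1.7% to 2.3% at a nominal 1% with equal clinic sizes. With G/(G-1) and t(29), the 1% figure is 1.0% to 1.2% for similar-sized clinics and 1.2% to 2.0% under assumed size CVs of 0.4 to 0.8; the upper end also needs an assumed autocorrelation of 0.8. Kauermann-Carroll with t(28) holds 0.9% to 1.1% for equal clinics and stays below 1.6% in the worst setting run.

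These figures rest on seven windows, ICC 0.20 and a clinic-level random or fixed effect, with working independence giving the top of the 1% range. They hardly depend on whether 132 or 33 clients per clinic-window is used. They do not show that the trial will be analysed without a correction.

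**What to change.** In Analysis and power, replace the unqualified phrase with: *bias-corrected cluster-robust standard errors (Kauermann-Carroll or CR2), with a t reference on clinics minus 2 (28) or Satterthwaite degrees of freedom*. State the significance level of the analysis in the same place. A permutation test that reassigns clinics to steps within the two randomisation strata (downstate and rest of state) is a useful optional check, particularly if clinic sizes prove very uneven, where even the corrected test ran slightly above its level.

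The cost is one sentence and a software option. The t reference alone widens a 99% interval by about 7% (2.763/2.576 = 1.073) and a 95% interval by about 4.5% (2.048/1.960 = 1.045), with a little more from the bias correction. On the t reference, the detectable retention difference goes from 2.8 to about 3.0 points. If the full protocol or SAP already specifies such a correction, no change of method is needed and the article should simply state it.

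### The detectable differences for medication initiation (6.7%) and ED visits (3.9%) cannot both follow from the one set of inputs printed for them

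*Protocol article*

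**What the plan says.** The Analysis and power section of the protocol article names one source for its power figures: "we drew from methods developed by Hussey and Hughes [80] as implemented in a Stata command, stepped wedge". It then fixes common parameters, "we computed detectable differences for a β = 0.80, α = 0.01, ICC/ρ = 0.20", for a "SW-RCT with 6 crossover points, and 5 clinics randomized at each point". Three outcomes follow:

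| Outcome | Cluster size m | Base rate μ | Stated detectable difference |
|---|---|---|---|
| 6-month retention | 132 | 0.25 | 2.8 pp |
| Medication initiation | 40 (Medicaid clients with OUD) | 0.40 | 6.7% |
| ED visits | 79 (Medicaid clients) | 0.40 | 3.9% |

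For initiation the wording is "and find a detectable difference of 6.7" per cent; for ED visits, "and find a detectable difference of 3.9" per cent. For retention, sensitivity analyses over ICC 0.10 to 0.30 and power 0.90 "found detectable differences ranging from 2.6 to 3.2" per cent. The paragraph concludes that power is sufficient for moderate and clinically meaningful differences.

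**The concern.** Initiation and ED visits share every printed input except m. In a Hussey-Hughes calculation with an ICC of this size, the detectable difference is very nearly proportional to 1/√m, so roughly doubling m should shrink it by a factor of about 1.4. The printed figures shrink by 1.72. The method is fully specified by the text for this comparison, so the mismatch is not explained by detail that an article leaves to a longer protocol.

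Both outcomes are named under Aim 1, and their detectable differences are part of the stated support for the power claim. As printed, a reader cannot tell which cluster sizes, base rates or results the sponsor actually worked with.

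**Working it through.** **Inputs.** From Analysis and power: I = 30 clinics (6 × 5), ρ = 0.20, α = 0.01, and the m and μ in the table. The article writes β = 0.80; I read this as power. My assumptions: two-sided α, one baseline period (so T = 7), and m as clients per clinic per period. Step 1 tests these assumptions.

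**Formula (Hussey-Hughes).** With σ² = μ(1−μ)(1−ρ)/m and τ² = ρμ(1−μ),

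Var(θ) = Iσ²(σ² + Tτ²) / [(IU − W)σ² + (U² + ITU − TW − IV)τ²],

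and the detectable difference is (2.576 + 0.842) × SE = 3.417 × SE.

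For six steps of five clinics and T = 7: U = 105, W = 2275, V = 455. Hence IU − W = 875 and U² + ITU − TW − IV = 11025 + 22050 − 15925 − 13650 = 3500.

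**Step 1: the article's own retention figure.** σ² = 0.1875 × 0.8/132 = 0.001136; τ² = 0.0375. SE = 0.00824, and the detectable difference is 2.82 pp against 2.8 stated. Changing one parameter at a time gives 2.98 (ρ = 0.10), 2.64 (ρ = 0.30) and 3.18 (power 0.90), which matches the stated 2.6 to 3.2. The setup is therefore calibrated on the article's own numbers. Reading m as a step total spread over five clinics would give 6.3 pp for retention, so that reading is ruled out.

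**Step 2: the other two outcomes in the same setup** (τ² = 0.048 for both).

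- Initiation: σ² = 0.24 × 0.8/40 = 0.0048. Var = 0.144 × 0.3408/(4.2 + 168) = 0.000285, SE = 0.01688, detectable difference **5.77 pp** (stated 6.7). Power at 6.7 pp: Φ(0.067/0.01688 − 2.576) = 91.8%.
- ED visits: σ² = 0.24 × 0.8/79 = 0.00243. Var = 0.000145, SE = 0.01204, detectable difference **4.12 pp** (stated 3.9). Power at 3.9 pp: Φ(0.039/0.01204 − 2.576) = 74.6%.

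**Step 3: the ratio, in which α and power cancel.** Expected: about √(79/40) = 1.41; the calibrated setup gives 5.77/4.12 = 1.40. Stated: 6.7/3.9 = 1.72, or 1.68 to 1.75 allowing for rounding (6.65/3.95 to 6.75/3.85). With T = 7 the ratio runs from 1.36 to 1.40 for ICC 0.01 to 0.50. The largest ratio was 1.44 over a grid of 6 to 9 periods, one- and two-sided tests, α 0.01 and 0.05, power 0.80 and 0.90, ICC 0.05 to 0.30, three readings of ρ, baseline or averaged binomial variance, and an increase or decrease in ED visits. No combination brought both figures within 3% of those stated.

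**Step 4: other numbers of periods** (two-sided, other inputs as stated).

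| Periods | Retention (stated 2.8) | Initiation (stated 6.7) | ED visits (stated 3.9) |
|---|---|---|---|
| 7 | 2.82 | 5.77 | 4.12 |
| 8 | 2.70 | 5.53 | 3.94 |
| 9 | 2.61 | 5.35 | 3.82 |

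More periods bring ED visits to 3.9 but move initiation further from 6.7.

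**Step 5: what inputs would give the stated results at T = 7.** 6.7 needs m of about 30; no base rate yields it at m = 40, since the maximum, at μ = 0.50, is 5.9 pp. 3.9 needs m of about 88, or μ of about 0.31 with m = 79.

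**The case against.** The strongest reply concerns ED visits. The article's text does not give the number of periods (the design figure was not available to me). Eight is a reasonable count: one baseline window, six starts at six-month intervals, and a second six months for the last group, because CARE runs for a year. Eight periods give 3.94, which rounds to the stated figure, with power of about 79% at 3.9. One less usual variant comes close to two of the three figures: nine periods, one-sided, within-clinic variance not reduced for the ICC, averaged binomial variance, and ED visits taken as a decrease. It gives 2.75 for retention and 3.92 for ED visits, but 5.60 for initiation. So a reader might infer that the ED figure is simply too favourable, and the documents do not support that: it depends on an unstated number of periods. What stands is that no setup fits all three figures. At the stated α, power and ICC, none came within 0.1 pp of 6.7 for initiation; the nearest, about 6.5 to 6.6 and 6.9, put ED visits at 4.5 to 5.0.

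Two other stronger readings also go too far.

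- A reader might conclude that the claim of adequate power fails. It does not: retention reproduces, the initiation figure errs on the cautious side, and the ED shortfall is about 0.2 pp at most.
- A reader might set the 79 clients against about 33 OUD clients per clinic per half-year (2000/30/2) and call the input impossible. The article describes the 79 only as Medicaid clients, without the OUD restriction it attaches to the 40, so that comparison mixes populations.

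**Conclusion.** The point holds as an internal inconsistency: 6.7% and 3.9% cannot both follow from the common inputs printed for them, and at least one input or result is wrong. The ratio argument needs no assumption about sidedness, ICC definition or number of periods.

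The size of each individual error is conditional. If m, μ and seven two-sided periods are right, initiation is overstated by about 0.9 pp (6.7 against 5.8) and ED visits understated by about 0.2 pp (3.9 against 4.1). The errors run in opposite directions, so one misapplied common parameter does not explain them. A misprinted cluster size or base rate is as possible as a wrong result. The practical effect is modest: design, number of clinics and broad power conclusion are unchanged.

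**What to change.** Re-run all three detectable differences from one script. State the number of periods and the sidedness used next to the results. Then do one of the following:

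- replace the two results, with about 5.8% for initiation and 4.1% for ED visits if m = 40, m = 79 and seven two-sided periods are kept; or
- if a different m, μ or ICC was used for either outcome, correct the printed input and say so.

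The cost is a few corrected numbers and one added clause. Nothing in the design or analysis needs to change.

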## Discussion

This study will provide a robust examination of the implementation of a measures-driven QI approach for SUD treatment. We will be able to provide insight into whether a multicomponent intervention that includes clinical training, training and support on QI processes, external facilitation, and an electronic client outcomes monitoring system improves quality and recovery outcomes. The study benefits from a strong academic-state partnership, an external facilitation model guided by the i-PARIHS implementation science framework, multiple sources of data to examine impacts of the intervention, as well as tools and trainings developed with input from a variety of stakeholders and a pilot during the first phase of this project.

The study team is currently finalizing clinic recruitment and randomization with plans to start the first five clinics in the intervention in December 2020 and January 2021. The ongoing COVID-19 pandemic has forced a shift in SUD treatment service delivery, which has traditionally relied heavily upon in-person services. Outpatient treatment clinics have had to rapidly and fundamentally change their service delivery models due to physical distancing mandates and new COVID-19 safety protocols. For example, programs have needed to change their work flows to accommodate telepractice for induction and management of medications for OUD, provide individual and group counseling via telemedicine, reduce reliance on drug screening (i.e., toxicology testing), and employ new strategies for treatment engagement. Therefore, while the pandemic continues, this study will not only have to adjust some of its facilitation and training activities to be done remotely rather than in-person, but we will also tailor facilitation to assist clinics in improving quality of care in the context of COVID-19 shifts in service delivery and workflows. We will carefully document changes to our protocols and clinic procedures as the COVID-19 pandemic continues to affect NYS and our participating project sites.

While there are a number of strengths in this study, we acknowledge the following possible exogenous and endogenous threats to validity. First, administrative data is incomplete. We rely significantly on administrative data to increase the efficiency of our research study that tests the impact of CARE in 30 clinics on treatment quality measures (e.g., pharmacotherapy use, retention) and outcomes (e.g., relapse). While there is strong precedent for using administrative data for research [99–106], these data will not capture all aspects of client experience (e.g., substance use, social consequences). To address the limitation, we are using a mobile platform that allows for collection of research data from a subsample of participants. These data will allow us to further study the intervention impact on recovery outcomes not captured in the administrative data.

In addition, there may be variability in the effect of the intervention due to variation in individual clinic capacity to integrate QI practices within their organizational structure. It will be critically important for future dissemination efforts to understand factors implicated in the implementation of CARE. While the study has adequate statistical power to detect a main effect, it will be important to understand the variability in effect across clinics. To address this, we will incorporate the embedded mixed-methods component of the study examining staff experiences. Additionally, we will explore potential intervention-related factors by conducting a series of post hoc analyses.

Finally, though the SW-RCT design offers a number of benefits, clinics will be randomized to step at the start of the trial with start dates staggered across 3 years. Therefore, it may be challenging to retain recruited clinics in the study while they wait to start the intervention. To reduce clinic attrition, we will employ strategies recommended in the stepped-wedge trial literature (e.g., keep recruited sites informed of progress, hold regular pre-intervention meetings) [107]. Also, recruited clinics will sign a study agreement indicating they understand the randomization procedures and timeline.

In summary, SUD clinics are under pressure to transition into a system that values quality metrics and outcomes. However, the workforce has been under-resourced and undertrained in processes that could assist them in making systemic changes to improve clinic functioning and client outcomes. This study will provide the field with a strong test of a multicomponent intervention to improve providers’ capacity to make systematic changes tied to quality metrics. The study will also result in training and materials that can be shared widely to improve QI implementation and clinical practice in the SUD treatment system.

